#### 10. Systemic immune status

Main analysis Immune status at 18 months measured in stimulated whole blood as cytokine release (combined assessments by principal component analyses)

Secondary analyses Composition of immune cell subsets in whole blood at birth and at 18 months of age

[Time Frame: 18 months]

#### 11. Airway mucosal immune status

Immune status measured in airway mucosal lining fluid at 4 weeks and 2 years of age (combined assessments by

principal component analyses for each age point)

[Time Frame: 4 weeks and 2 years]

#### 12. 17q21 genotype and sphingolipid metabolites

In a secondary analyses, we will determine the effect of 17q21 genotype on the efficacy of vitamin D supplementation in the prevention of asthma/wheeze. We will compute hazard ratios for the reduction in asthma/wheeze risk associated with prenatal supplementation, stratified by rs12936231. rs12936231 is a functional SNP influencing expression of ORMDL3, and given the role of ORMDL3 as a key sphingolipid biosynthesis regulator, we will subsequently investigate the relative abundance of sphingolipids between those in the vitamin D Intervention arm and those in the placebo group, stratified by 17q21 genotype. Finally we will identify interactions between prenatal vitamin D supplementation, rs12936231 genotype and sphingolipid metabolism in the risk of asthma/wheeze by age three.

[Time Frame: 6 months]

#### 13. Dental health

Caries and enamel defects (molar incisor hypomineralization, MIH) determined at a dental examination at age 6 years.

[Time Frame: 6 year]

#### Other Pre-specified Outcome Measures:

##### 14. Asthma

Asthma diagnosed from age 3 to 10 years based on the same predefined algorithm of recurrent troublesome lung symptoms, response to treatment after withdrawal of treatment, which was used for persistent wheeze at age 0-3 in phase 1 of the study. Primary outcome in phase 2 is current asthma at specific visits till age 10 years, which is diagnosed in children fulfilling the persistent wheeze algorithm at any point during the first 10 years of life and still needing inhaled corticosteroids at specific visits (3, 4, 5, 6, 8 and 10 years of age) to control the symptoms.

##### Asthma exacerbations:

Age at onset and number of severe asthma exacerbation diagnosed by predefined criteria of acute severe asthma requiring oral/ high dose inhaled steroids or acute hospital contact

[Time Frame: 3-10 years of age]

##### 15. Lung function measurements

Spirometry measuring airflow assessed by FEV1, MMEF and FEV1/FVC ratio at age 5, 6, 8 and 10 years and airway resistance (sRaw) measured by plethysmography at age 3, 4, 5, 6, 8 and 10 years. Multiple breath wash-out using SF6 and N2 as inert gasses to determine LCI, Scond and Sacin at ages 3, 4 and 5 years.

Bronchial reactivity: [Time Frame: at 6 years of age] Provocative dose of methacholine leading to a 20% drop in FEV1 from baseline (PD20 value) at age 6 years.

Airway inflammation: [Time Frame: 6-10 years of age] Measurement of fractional exhaled nitric oxide (FeNO) at age 6, 8 and 10 years

[Time Frame: 3-10 years of age]

## 16. Infections

Prescribed medicine for infections. Types and length of infections

[Time Frame: 3-10 years of age]

## 17. Growth

Anthropometrics:

Clinical follow up on the development of weight in kg (calibrated digital weight scales), height in cm (Harpender stadiometer), waist-, thorax- and head circumference in cm (using tape; 3 times each) at every visit till age 10 years assessed longitudinally in the research clinic.

Body composition:

Body composition measured as fat mass, lean mass, bone mineral content (BMC) and bone mineral density assessed (BMD) by DXA scans at 6 years of age.

Body impedance measurements at 10 years of age.

[Time Frame: 3- 10 years of age]

## 18. Cognitive function

The following cognitive functions will be covered by paper-and-pencil-tests:

- The verbal memory.
- The Vocabulary and Matrices subtests from (WISC-IV) to estimate intelligence.
- Verbal working memory.
- Processing speed.
- Mental flexibility..
- Fine motor dexterity will be assessed with the Grooved Pegboard Test

The following cognitive functions will be assessed using the Cambridge Neuropsychological Test

Automated Battery subtests:

- Sensorimotor functioning.
- Mental response speed and motor speed will be assessed with the Reaction Time task;
- Working memory capacity.
- Working memory and strategy formation.
- Attentional set formation, maintenance, shifting, and flexibility of attention.
- Response inhibition.
- Visual learning and memory.
- Sustained attention.
- Facial affect recognition.

[Time Frame: 10 years of age]

#### 19. Behavioral and psychopathological dimensions.

Questionnaires will be administered to the parents. ADHD-RS questionnaire at 8 and 10 years of age. Strength and Difficulties Questionnaire (SDQ) at 6, 8 and 10 years of age. Social Responsive Scale, Second version (SRS-2) at 10 years of age. The Behavior Rating Inventory of Executive Function 2nd edition (BRIEF-2) at 10 years of age. The Child Behavior Checklist school-age version (CBCL) at 10 years of age. Behavioral and psychopathological dimensions will be assessed at 10 years of age with the semi-structured clinical interview Schedule for Affective Disorders and Schizophrenia for School-Age Children - Present and Lifetime Version (K-SADS-PL) first with a parent and next with the child.

The child assessor will rate potential behavioral and emotional problems observed during the cognitive test session using the Test Observation Form (TOF).

The Magical Thinking Questionnaire (MTQ) will be given to the child.

[Time Frame: 6- 10 years of age]

#### 20. MRI scanning of the Brain

Following technics will be used. Structural MRI scanning to distinguish between grey and white matter. Diffusion weighted imaging to register the fiber directions in the brain. Magnetisation transfer imaging to measure the magnetisation transfer ratio reflecting the interaction between macromolecular protons and the free water protons of tissue, and this technique in addition to quantitative T1-mapping will be used to assess myelination in the developing brain.

Magnetic resonance spectroscopy (MRS) allows for non-invasive measurement of metabolites.

Phase-contrast MR angiography to detect the total cerebral blood flow. Arterial spin labelling to measure cerebral blood perfusion.

[Time Frame: 10 years of age]

#### 21. Eczema

Age at onset of eczema diagnosed prospectively by research doctors according to predefined algorithm based upon Hanifin and Rajka criteria and severity determined by SCORAD score. In phase 2 current eczema at specific visits till age 10 years will be evaluated.

[Time Frame: 3-10 years of age]

#### 22. Allergic sensitization/atopy

Allergic sensitization at 6 and 10 years of age assessed by skin prick test (ALK-Abelló, Denmark) and specific IgE in blood (ImmunoCAP, PHarmacia Diagnostics AB, Sweden) and total-IgE level and blood eosinophil count measured at the same timepoints.

[Time Frame: 3-10 years of age]

#### 23. Airway mucosal immune status

Immune status measured in airway mucosal lining fluid at 3, 6 and 10 years of age (combined assessments by principal component analyses for each age point).

[Time Frame: 3-10 years of age]

#### 24. allergic rhinitis

Allergic sensitization combined with symptom recording of troublesome congestion or sneezing or runny nose upon relevant exposure to allergens at age 3, 4, 5, 6, 8 and 10 years.

[Time Frame: 3-10 years of age]

Overview of clinical tests; phase 2:

| Children                      | 4 years | 5 years | 6 years | Investigations of biologic material            |
|--------------------------------------|----------------|----------------|----------------|-------------------------------------------------------|
| Airway and eczema diary              | x              | x              | x              |                                                       |
| Doctor examination                   |                |                | x              |                                                       |
| Tympanometry                         |                |                | x              |                                                       |
| Blood pressure                       |                |                | x              |                                                       |
| Growth details                       | x              | x              | x              |                                                       |
| Nose filter                          |                |                | x              | Immune system                                         |
| Electronic nose measure              |                |                | x              | Exhaled air                                           |
| Urine sample                         |                |                | x              | Interleukins, leukotrienes and metabolic products     |
| Blood sample                         |                |                | x              | Immune system, epigenetics and metabolic product      |
| Skin prick test                      |                |                | x              | Allergy                                               |
| Hair sample                          |                |                | x              | Cotinine (nicotine product)                           |
| Faeces sample                        | x              | x              | x              | Microbiological colonization                          |
| Skin swab                            |                |                | x              | Microbiological colonization                          |
| Throat swab                          |                |                | x              | Microbiological colonization                          |
| Nasal scrape*                        |                |                | x              | mRNA - gene expression                                |
| Activity measure                     |                |                | x              |                                                       |
| DXA scan                             |                |                | x              | Lean mass, fat mass and bone mineral content/ density |
| Spirometry                           |                |                | x              |                                                       |
| Bodybox                              | x              |                | x              |                                                       |
| Multiple breath washout              | x              |                | x              |                                                       |
| Metacholine provocation*             |                |                | x              |                                                       |
| FeNO measure*                        |                |                | x              |                                                       |
| Child Behavior Checklist*            |                |                | x              | Mentality and behavior                                |
| Parents                       |                |                |                |                                                       |
| Interview - child environment        | x              | x              | x              |                                                       |
| Interview - child asthma and allergy | x              | x              | x              |                                                       |

\*New tests

## SUMMARY OF CHANGES

Changes to the original protocol are indicated in <https://clinicaltrials.gov/ct2/show/NCT00856947>.

Briefly, these encompass introduction of novel assessments, including neurological development, growth, systemic immune status and airway mucosal immune status.

Growth: Dual X-ray Absorptiometry (DXA) scans are performed to measure the child's pre- and postnatal factors which play a role in the development of lean mass, fat mass and bone mineralization. The prevalence of obesity and osteoporosis is a growing epidemic in the Western societies and adult obesity is associated with growth in childhood. Despite osteoporosis being characterized as a condition among the elderly population it is well-known that predisposition occurs during childhood. Therefore, we examine the children's growth and bone mineralization, and the key factors influencing these outcomes.

## **2. Original statistical analysis plan, final statistical analysis plan, summary of changes**

### **ORIGINAL STATISTICAL ANALYSIS PLAN**

#### **Outcome definitions:**

##### Primary outcome

Persistent wheeze: Age at onset of persistent wheeze diagnosed according to a predefined algorithm of recurrent troublesome lung symptoms, response to treatment and relapse after withdrawal of treatment

##### Secondary outcomes

Asthma exacerbations: Age at onset of severe asthma exacerbations diagnosed by predefined criteria of acute severe asthma requiring oral/high dose inhaled steroids or acute hospital contact

Eczema: Age at onset of eczema diagnosed prospectively by research doctors according to predefined algorithm based upon Hanifin and Rajka criteria

Allergic sensitization: Allergic sensitization at 6 and/or 18 months of age assessed by skin prick test and specific IgE in blood

Infections: Main analysis: Number of lower respiratory tract infections registered in daily diaries  
Secondary analyses: Acute otitis media, number of upper respiratory tract infections, number of other infections, total number of infections

Mothers levels of 25-OH-Vitamin D, PTH, Calcium, alkaline phosphatase

Growth: Anthropometric measurements in the clinic.

Body composition (fat mass and bone mineral density) assessed by DXA scan at 3 years of age  
Development of BMI from birth to 3 years assessed longitudinally in the research clinic

#### **Statistical analyses:**

The effect of high-dose Vitamin D3 supplementation on age at onset of persistent wheeze, lower respiratory infections, and eczema is analyzed by Cox proportional hazards regression, where p-values correspond to Wald tests. The children are retained in the model from birth until age of diagnosis, drop out, or age at their last clinic visit before the RCT was unblinded.

The effect of Vitamin D3 supplementation on the cross-sectional end-points asthma and allergic sensitization is analyzed by logistic regression, whereas the effect on number of wheezy episodes and upper respiratory infections is analyzed by a generalized estimating equation (GEE) Poisson regression model.

The effect on airway immunology is analyzed by calculating geometric mean ratios of each mediator in the high-dose Vitamin D3 vs. control group and by a principal component analysis (PCA) capturing the overall immunological trends in the data and their relation to the intervention analyzed by Wilcoxon rank sum test. Initially, the mediator levels were log-transformed. Prior to the PCA the variables were scaled to unit variance.

The primary analysis of persistent wheeze is presented crude and adjusted for sex, birth season, maternal Vitamin D level at randomization, and the n-3 LCPUFA RCT.

A significance level of 0.05 is used in all types of analyses.

Additional secondary endpoints:

The novel assessments introduced in the cohort resulted in additional secondary end-points:

Airway mucosal immune status

Description: Immune status measured in airway mucosal lining fluid at 4 weeks and 2 years of age (combined assessments by principal component analyses for each age point)

Systemic immune status

Description:

Main analysis: Immune status at 18 months measured in stimulated whole blood as cytokine release (combined assessments by principal component analyses)

Secondary analysis: Composition of immune cell subsets in whole blood at birth and at 18 months of age

Neurological development 0-3 years

Description:

Main analysis: Cognitive development assessed at 2½ years using the cognitive part of Bayley Scales of Infant and Toddler Development, third edition

Secondary analyses: 1) Milestone development monitored prospectively by the parents using a registration form based on The Denver Development Index and WHO milestones registration (combined assessment by principal component analysis); 2) Language development assessed at 1 and 2 years of age with the Danish version of The MacArthur Bates Communicative Developmental Inventory (CDI); 3) The child's general development (language, fine and gross motor, social and problem solving) at 3 years of age assessed with Ages and stages Questioner, third edition (ASQ-3)

Growth:

Body composition: Body composition measured as fat mass, lean mass, bone mineral content (BMC) and bone mineral density assessed (BMD) through DXA scans at 6 years of age.

Anthropometrics: Clinical follow up on the development of weight in kg (calibrated digital weight scales), height in cm (Harpender stadiometer), waist-, thorax- and head circumference in cm (using tape; 3 times each) at every visit till age 10 years assessed longitudinally in the research clinic.

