## **Method and trial procedure**

The women are recruited from the COPSAC2010 cohort; Local Ethics Committee (H-B-2008-093), Danish Data Protection Agency (2015-41-3696).

The study is a double-blinded, placebo-controlled, randomized parallel group design. 800 pregnant women will be randomized in a 1:1 ratio to intake of either high dose vitamin D supplementation or placebo according to one of the following regimes:

- 1) Placebo (+ guidance in recommended supplement of vitamin D (400 units daily)) or
- 2) High dose vitamin D supplement (2400units daily) (+ guidance in recommended supplement of vitamin D (400units daily))

The regimes are administered orally as 2 tablets daily.

Blinding and randomization are carried out by the Capital Region Pharmacy and stratified according to treatment group in the fish oil intervention study (ClinicalTrials.gov: NCT00798226). This allows for equal numbers receiving high dose vitamin D supplementation in both the fish oil active group and the fish oil placebo group.

The intervention is initiated at the beginning of the third trimester (pregnancy week 24) and continued until 1st visit to the COPSAC clinic after birth at week 1-2 postpartum. At the clinical visit in pregnancy week 24, the women will be provided with the intervention treatment and interviewed about current daily vitamin D intake and history of diseases likely to influence vitamin D levels. At pregnancy week 36 adherence to the regime will be assessed by interview at the COPSAC clinic. Furthermore, the women will be instructed to return the remaining tablets at the end of the intervention for evaluation of their compliance.

At pregnancy week 24 and 1st visit after birth a blood sample will be drawn from the mother in order to measure 25-OH-vitamin D, total calcium, parathyroid-hormone (PTH) and alkaline phosphatase.

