### **Study Description**

#### **Brief Summary:**

The aim of this study is to prevent asthma symptoms (recurrent wheeze) in childhood by supplementation with high dose vitamin D to the mother during pregnancy. Participants are mothers and children of the ABC (Asthma Begins in Childhood) cohort. Mothers are recruited during pregnancy and receive daily supplement with 2400 IU of Vitamin D3 or placebo from week 24 of gestation to 1 week after delivery. In addition all mothers are advised to take the recommended dose of 400 IU vitamin D daily. The mothers in ABC also participate in an interventional trial with fish oil supplementation, and the vitamin D randomization is stratified by fish oil treatment group. The child is followed with acute and planned visits at the research unit, and wheeze is diagnosed according to predefined algorithms.

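### The airway immune component scores are tested without the fish-oil stratum or the plan's own covariates: a valid test, but less precise than the design allows

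*Supplement*

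**What the plan says.** **Endpoint.** The latest protocol lists airway mucosal immune status as secondary outcome 11: "Immune status measured in airway mucosal lining fluid at 4 weeks and 2 years of age", summarised by principal components at each age.

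**Analysis.** The original SAP (Statistical analyses) gives two analyses. One is "calculating geometric mean ratios of each mediator in the high-dose Vitamin D" arm against control. The other is a principal component analysis of the log-transformed, unit-variance mediators, with "their relation to the intervention analyzed by Wilcoxon rank sum test". Neither mentions a stratum, a covariate or a confidence interval.

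**Design.** Randomisation was "stratified according to treatment group in the fish oil intervention study" (Method and trial procedure). The Brief Summary repeats that "the vitamin D randomization is stratified by fish oil treatment group". No other stratification factor is named. The stated purpose is balance: "This allows for equal numbers receiving high dose vitamin D supplementation in both the fish oil active group and the fish oil placebo group".

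**Adjustment elsewhere.** The same SAP section says: "The primary analysis of persistent wheeze is presented crude and adjusted for sex, birth season, maternal Vitamin D level at randomization", and adds the n-3 LCPUFA trial as a fourth adjuster. The SAP for the current study (Statistics) adjusts all its analyses for these four variables and reports 95% confidence intervals, but it describes neurodevelopmental outcomes only. Its Summary of changes presents it as an addition to the original plan. The original text is therefore the only place where a test for the airway endpoint is specified.

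**The concern.** Fish oil is an active co-intervention that may itself move immune mediators. If it does, an unstratified comparison of the vitamin D arms leaves the fish-oil difference in the error term, although the randomisation has already balanced it. The test is then slightly conservative and somewhat less powerful than the design permits. The same holds for any prognostic value in sex, season of birth and maternal vitamin D, which the plan already intends to use for wheeze.

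Precision on one secondary endpoint is at stake, together with consistency: the airway components would be analysed crude, while wheeze and the neurodevelopmental outcomes, including milestone components, are adjusted for the same four variables.

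**Working it through.** **Inputs from the documents.** Allocation: "800 pregnant women will be randomized in a 1:1 ratio", balanced within fish-oil arm. Significance level: 0.05, taken as two-sided as in the current-study SAP. The documents give no number of children with airway samples, no SD, effect size or power for this endpoint, and no association of any covariate with a mediator. There is therefore no planned figure to reproduce.

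**Assumed inputs.** About 503 children (borrowed from the Bayley power paragraph, so only illustrative), two equal fish-oil strata, 1:1 allocation within each, and normally distributed scores. The true vitamin D effect is set where an unadjusted t-test has 80% power: (1.960 + 0.842) × 2/√503 = 0.25 SD.

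**Step 1: type I error of the unstratified test.** If fish oil shifts the score by d within-stratum SDs, the pooled variance is too large by the factor 1 + d²/4. The large-sample type I error is 2 × [1 − Φ(1.96 × √(1 + d²/4))].

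- d = 0.2: factor 1.010, type I error 4.9%
- d = 0.3: factor 1.023, type I error 4.7%
- d = 0.5: factor 1.063, type I error 4.3%

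**Step 2: gain from stratifying alone.** Simulation with 504 children and 4,000 runs per scenario:

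| Fish-oil shift (SD) | Crude Wilcoxon, type I error | Crude Wilcoxon, power | van Elteren, power |
|---|---|---|---|
| 0 | 4.8% | 78.0% | 77.5% |
| 0.2 | 4.7% | 77.3% | 77.9% |
| 0.5 | 4.9% | 76.1% | 77.6% |
| 1.0 | 2.9% | 69.4% | 76.6% |

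Up to 0.5 SD the gain is about 0 to 2 points. It reaches about 7 points only at 1.0 SD, an extreme value. The simulation standard error near 5% is √(0.05 × 0.95/4,000) = 0.34 points. At 0.5 SD the crude rate (4.9%) lies above the formula's 4.3%, but the stratified and linear-model tests also ran high in that scenario's null runs (both 5.7%), so this looks like simulation noise.

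**Step 3: gain from covariates.** If the covariates explain a share R² of the variance, adjusting is equivalent to a sample of N/(1 − R²).

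| Assumed R² | Extra children, 1/(1 − R²) − 1 | Equivalent of 503 | Adjusted linear model, simulated power | Crude Wilcoxon, simulated power |
|---|---|---|---|---|
| 5% | 5% | 529 | 81.6% | 78.0% |
| 10% | 11% | 559 | 84.0% | 78.0% |
| 20% | 25% | 629 | 88.4% | 78.3% |

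The power columns take a fish-oil shift of 0.2 SD. About 2 points of each difference come from using a linear model on normal data rather than from the covariates: the rank test's efficiency of 3/π gives 78.2% where the t-test has 80.0%.

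**The case against.** The strongest case for leaving the plan alone has several parts.

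- **Validity.** Stratified randomisation does not oblige a stratified test. Vitamin D is balanced within fish-oil arms by design, so fish oil cannot systematically confound the comparison, and the error rate stays at or below nominal. This stands. A reader might infer that the test is wrong because it ignores the design. The documents do not support that; the point concerns precision only.
- **Strength of the covariates.** A reader might assume that the listed variables are strong predictors. Nothing in the documents says how any of them relates to an airway mediator. The larger gains in step 3 rest wholly on an assumed R².
- **Effect sizes.** It is tempting to say that the endpoint yields only a p-value. That is true of the component test, but the same sentence also plans geometric mean ratios, which are interpretable effect sizes. A component score has no natural unit, so a mean difference on it adds less.
- **Choice of a rank test.** Logging and scaling the mediators does not make component scores normal or free of outliers. A rank test is defensible, which is why the fix keeps one.
- **Status of the text.** The wording stands in the original SAP, and no sentence states that it is still in force. This is an inference, but a fair one: the outcome is in the latest listing, the later SAP describes itself as an addition, and nothing replaces the airway method.
- **Silence.** The plan never calls the ratios crude; it states no adjustment. It is equally silent for other secondary outcomes. The gap is therefore not peculiar to this endpoint, but that does not close it here.
- **Timing.** Changing a test after unblinding is not free. This stands and shapes the fix.

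**Conclusion.** The point holds as a matter of efficiency and consistency on a secondary endpoint. As written, the component scores are compared without the randomisation stratum and without covariates, and no adjustment is stated for the geometric mean ratios, although the plan already names four suitable baseline variables for wheeze. The planned test is valid and at worst mildly conservative (4.9% to 4.3% by formula for assumed fish-oil shifts of 0.2 to 0.5 SD).

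The loss may be negligible or material, and the documents cannot settle which. Omitting the stratum costs about 0 to 2 power points over that assumed range. Omitting the covariates costs the equivalent of 5% to 25% of the sample if R² lies between 5% and 20%. The power figures also assume about 503 children and normal scores. None of this suggests a false-positive risk.

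**What to change.** Amend the airway immunology paragraph of the SAP as follows.

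1. Test each component score with the Wilcoxon test stratified by fish-oil arm (van Elteren).
2. Report each mediator's geometric mean ratio with a 95% CI from a linear model of the log mediator on vitamin D arm, adjusted for sex, birth season, maternal vitamin D at randomisation and n-3 LCPUFA allocation.
3. Optionally, add a linear model of each component score with the same four variables.
4. State how children with a missing baseline vitamin D value are handled, since adjusted models would otherwise drop them.

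This costs a few sentences and a few lines of code. All four variables already belong to the plan, so no new data are needed. If unblinded airway results already exist, document the change as an amendment and show the new analysis beside the planned unstratified Wilcoxon result, not in its place.
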